HIV infection is widely acknowledged as the driving force behind the current TB epidemic in Southern Africa. Long term control of TB must include addressing the problem of HIV prevention. Proven interventions to reduce the incidence of HIV at a community level are disappointingly few. Provision of voluntary counselling and testing (VCT) has been promoted as an important step in supporting individuals to change behaviour by facilitating knowledge of HIV status. Few trials have used HIV incidence as an end point, although a recent study in Harare among factory workers showed that despite good uptake of VCT HIV incidence was not reduced[6]. Other studies have shown some evidence of behaviour change in HIV-positive individuals but little change has been seen in HIV-negative ones[7]. VCT has been shown to be most effective when offered to couples, since this allows discordant couples to make realistic plans to reduce the risk of HIV transmission[8,9]. Antiretroviral drugs are rapidly becoming more available in developing countries and it is hoped that the increased availability of these drugs may increase uptake of HIV testing and counselling and also reduce transmission of HIV by reducing viral load. This theory is unproven, however, and in wealthier countries, already using antiretrovirals, there is evidence that sexual behaviour has become more, rather than less, risky since their use became widespread and that HIV incidence may be increasing[10].

Finally, stigma is recognised as a barrier for individuals to access diagnosis and care for both TB and HIV. Studies have demonstrated that stigma prevents people (including TB patients or suspects) from: accessing health care, learning their HIV status, disclosing their HIV status to partners, changing unsafe behaviour, and caring for people living with HIV/AIDS (PLWHA), and that the most extreme forms of stigma are often found in households and health facilities [11].

ZAMSTAR has addressed these issues by developing two interventions that combine all of the above strategies and that can be applied at community level. These interventions are community-based enhanced case finding for tuberculosis (ECF) and household counselling and provision of combined TB/HIV prevention services at the household level (HH). The effectiveness of these interventions at population level will be evaluated through a community-randomised trial with a 2 × 2 factorial design.

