### Outcome measurement

#### Baseline assessment of communities

In order to stratify and restrict the randomisation of communities a baseline assessment was conducted by collating information on TB notification rates, TB treatment outcomes, HIV prevalence data and the prevalence of tuberculous infection in school children (see below). In addition to the quantitative baseline assessment, a rapid qualitative appraisal of the communities was conducted. This appraisal involved community mapping, observation and key informant interviews to understand the domains of TB in the local community including population movement, congregation points, beliefs and knowledge about TB and HIV as well as general socio-economic information about the communities

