### Randomization

Due to the small number of communities in the study we stratified randomisation by country and the prevalence of TB infection (as measured by baseline TST surveys and categorised as high/low within countries). We used restricted randomisation to ensure balance on TST prevalence, HIV prevalence, urban/rural, social context and geographical location. A two-stage public randomisation ceremony was conducted to select one of the possible allocations for the study arms and then to allocate the interventions to those study arms. The design and results of this allocation procedure have been described in another paper [18].

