Apart from calculation of crude effects, adjusted analyses to account for potential confounding effects will also be performed. Potential confounding factors will include age, sex, TB infection prevalence (as calculated by baseline TST surveys) as well as other factors found to differ between study arms at baseline and which may be risk factors for a particular outcome. For the binary outcomes (prevalence, incidence) logistic regression will be used to adjust for confounders at the individual level and cluster level, adopting a two-stage process. The regression model will include terms for the adjustment factors and strata, but not study arm. For each community the fitted model will be used to obtain the ratio of observed (O) to expected (E) or O/E events, and a log transformation applied to this ratio where appropriate. Linear regression of the log mean O/E on strata and arm (2-way ANOVA) will be used to estimate the risk/rate ratio and 95% CI associated with the intervention. The variance for the ratio of mean O/E is calculated from the residual mean square from an ANOVA of O/E on strata and arm.

For the continuous outcomes such as intervention costs and stigma levels, linear regression of the mean number/score will be used to adjust for confounders at the individual level. The regression model will include terms for the adjustment factors and strata, but not study arm. For each community the fitted model will be used to obtain the difference between observed and expected number of events. Linear regression of the difference O-E on strata and arm (2-way ANOVA) will be used to estimate the difference in (O-E) between arms and the 95% CI associated with the intervention. For all analyses, the robustness of the assumptions will be confirmed by a non-parametric stratified permutation test.

Analyses will also look at effects stratified by urban/rural classification, TB notification rates, ART usage, size of community and HIV prevalence. It is recognised that the study has low power to detect differences by subgroup and also the interaction between the interventions (ECF plus HH Vs standard TB/HIV control activities) and so the results of such analyses will be interpreted with caution.

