The small sample size also affected our choice of randomisation strategies. Stratification and restricted randomisation were necessary to ensure balance between the arms of the trial and to reduce the between-community coefficient of variation[22].

Despite these challenges the study is underway and the interventions appear to be feasible and popular. One of the study's strengths is that it is embedded within the existing health services, working closely with district and provincial health teams and with clinic staff. The variety of cultures and infrastructure ensures that the results will be generalisable and we can already see that the interventions could be applied in the routine health setting. The primary outcome of the study, TB prevalence, will not be measured until 2010, but already important knowledge is being generated that is helping us understand the complex epidemiology of the TB/HIV epidemic. The results of this trial will provide much needed evidence for health policy makers as they strive to control TB and HIV.

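### Choosing extra adjustment variables by baseline imbalance will normally miss HIV prevalence and urban/rural, which the restricted randomisation balanced, and so may forgo precision in the adjusted analysis

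*Protocol article*

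**What the plan says.** The Analytic plan describes a crude cluster-level analysis: regression of log community prevalence on strata and arm, with the interval taken from the residual mean square. It then adds adjusted analyses for possible confounding. The named covariates are introduced as "Potential confounding factors will include age, sex, TB infection prevalence (as calculated by baseline TST surveys", to which are added "other factors found to differ between study arms at baseline and which may be risk factors for a particular outcome". The two conditions in that last phrase are joined, so an observed difference between arms is necessary for entry. In the first of the two stages, "The regression model will include terms for the adjustment factors and strata, but not study arm".

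Under Randomization, "we stratified randomisation by country and the prevalence of TB infection", the latter split high/low within country. The same section says: "We used restricted randomisation to ensure balance on TST prevalence, HIV prevalence, urban/rural, social context and geographical location". The Discussion gives the purpose of stratification and restriction as "to ensure balance between the arms of the trial and to reduce the between-community coefficient of variation". HIV prevalence was among the baseline data, which came from "collating information on TB notification rates, TB treatment outcomes, HIV prevalence data and the prevalence of tuberculous infection in school children" (Baseline assessment of communities). On its role in the outcome, the Rationale says: "HIV infection is widely acknowledged as the driving force behind the current TB epidemic in Southern Africa".

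Elsewhere in the Analytic plan, HIV prevalence and urban/rural appear only as factors for subgroup analyses, which the protocol says have low power.

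**The concern.** The entry rule looks for imbalance, and the design set out to remove imbalance on HIV prevalence and urban/rural. A variable can be well balanced and still strongly prognostic. Balance lowers the true variability of the effect estimate, but the reported standard error falls only if the variable, or something that carries it, is in the model. Otherwise its variance remains in the residual mean square and the interval is conservative.

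The plan also treats restricted variables unevenly. TST prevalence was restricted and is adjusted for regardless. HIV prevalence was restricted, is described as the main driver of the epidemic, and is not named.

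With 24 communities, and between-community variation making up about half the variance of a community's log prevalence, several points of power could be at stake if the omitted variables are prognostic. Nothing is at stake if they are not.

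**Working it through.** **1. The plan's own figure.** Inputs from Sample size and Table 1: prevalence 1.0% against 0.7%, k = 0.20, 5,000 per community, 20% losses (m = 4,000), 80% power, two-sided 5%. The usual formula for unmatched clusters gives, per side,

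c = 1 + (1.960 + 0.842)² × [p0(1-p0)/m + p1(1-p1)/m + k²(p0² + p1²)] / (p0-p1)²

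= 1 + 7.849 × (2.475 + 1.738 + 5.960) × 10⁻⁶ / (9 × 10⁻⁶) = 9.87.

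The total is 19.7. Multiplied by 1.2 it is 23.7, which matches the stated 24. This variant also matches all ten table rows for k = 0.15 and k = 0.20.

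**2. What is in the adjusted model.**

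| Variable | Balanced by design | In the model |
|---|---|---|
| Country | stratum | always |
| TST prevalence | stratum (high/low) and restriction | always |
| Age, sex | not mentioned | always |
| HIV prevalence | restriction | only if found to differ |
| Urban/rural | restriction | only if found to differ |

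**3. What naming both variables in advance would change.** The planned prevalences are 1.0, 0.7, 0.7 and 0.49%. The within-community variance of log prevalence is about 1/(m p): 0.0250, 0.0357, 0.0357 and 0.0510, mean 0.0369. The between-community part is k² = 0.0400. The total is 0.0769, of which 52% is between communities. For 12 against 12, SE = √(0.0769/6) = 0.113. The effect is |ln 0.7| = 0.357, so the noncentrality is 3.15.

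Let R² be the share of between-community variance that the two variables explain. The documents give no value, so it is an assumption. The variance becomes 0.0369 + 0.0400 × (1 - R²), and two degrees of freedom are spent. The comparator has no covariates. Counting four strata and two interventions leaves 24 - 4 - 2 = 18 df. The plan states 16, so both are shown.

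| R² | CI half-width (18 to 16 df) | Power (18 to 16 df) | Change, points | Power (16 to 14 df) |
|---|---|---|---|---|
| not adjusted | reference | 84.6% | reference | 84.1% |
| 0 | +0.9% | 84.1% | -0.5 | 83.4% |
| 0.05 | -0.4% | 85.0% | +0.4 | 84.3% |
| 0.1 | -1.8% | 85.9% | +1.3 | 85.3% |
| 0.2 | -4.5% | 87.8% | +3.2 | 87.2% |
| 0.3 | -7.3% | 89.6% | +5.0 | 89.0% |
| 0.5 | -13.2% | 93.0% | +8.4 | 92.5% |

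The change pays for its degrees of freedom once R² reaches roughly 0.05. Other approximations to the within-community variance move the unadjusted power by 0.1 to 0.2 points.

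**4. Does the rule in practice miss the variables?** A simulation used 24 communities in four equal strata, a 2 × 2 factorial and 1,500 runs per setting. Two inputs are assumptions: a restriction limit of 0.25 SD on each variable, and p < 0.20 as the meaning of a difference. The rule selected either variable in at most 0.1% of runs.

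At R² = 0.4 with both effects present, the mean model SE was 0.118 against a true SD of 0.106. With both variables named in advance the mean SE was 0.102, and power was 90.9% against 85.1%. With no effect of either intervention, the analysis under the rule rejected in 2.5% of runs and the pre-specified one in 5.1%.

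**The case against.** Several points on the other side are sound.

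- **Status of the adjusted analysis.** A reader might infer that the imbalance rule governs the primary estimate. The article does not say so. It sets out a crude stratified analysis, then adds adjusted ones whose stated aim is control of confounding.
- **Exclusion.** A reader might infer that HIV prevalence and urban/rural are ruled out. They are not: the protocol does not define a difference, and restriction limits imbalance without necessarily removing it. The limits are in a separate paper that is not at hand. Omission is what one should expect, not what the text prescribes.
- **Other sources of precision.** It would be wrong to call these covariates the only way to reduce between-community variance. Strata, age, sex and TST prevalence are already modelled, and HIV prevalence may overlap with country and TST prevalence. The R² that matters is what is added beyond those, so the table's no-covariate comparator may flatter the gain.
- **Data dependence.** The selection uses baseline data, and the Discussion says TB prevalence will not be measured until 2010. The set can therefore be settled before outcomes are seen.
- **Direction of the error.** Intervals are too wide, not too narrow. Neither bias nor excess false positives can be inferred.
- **Place.** A final covariate list commonly belongs in the analysis plan. Here, though, the protocol states a selection rule, and that rule is the problem.

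The planned stratified permutation test does not clearly repair the intervals, since its description does not mention the restriction.

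What remains is a poorly chosen entry condition and uneven treatment of two restricted variables. The case is stronger for HIV prevalence, because the protocol says nothing comparable about urban/rural as a driver of TB.

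**Conclusion.** The point holds as one of efficiency. The stated rule makes imbalance a condition of entry and will normally pass over two variables that the allocation was built to balance, one of which the protocol itself regards as the main driver of the disease. If they are prognostic beyond the strata and TST prevalence, the adjusted interval is wider than necessary.

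The size rests on an R² that the documents do not supply: about half a point of power lost at zero, roughly 1 point gained at 0.1, 3 at 0.2, 5 at 0.3 and 8 at 0.5. This is under k = 0.20, 4,000 per community and a no-covariate comparator. The pattern is the same from the plan's 16 degrees of freedom. The downside is small and bounded, and the possible gain is larger, so the change is worth making.

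**What to change.** Before outcome data are available, replace the imbalance rule with a fixed list for the adjusted analysis of the primary outcome: age and sex at individual level, and baseline TST prevalence, baseline HIV prevalence and urban/rural at community level. If only one variable can be added, it should be HIV prevalence. Deduct one degree of freedom for each added community-level covariate from the number the plan states. Keep factors chosen because they differ at baseline for a sensitivity analysis labelled as such.

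The cost is a change of wording and about two degrees of freedom, with a slight loss of power (0.5 to 0.7 points in the calculation above) if the covariates turn out not to be predictive. No new data are needed: HIV prevalence was collated at baseline, and both variables were used in the restriction.

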### Sample size

Based on data from prevalence studies in Cape Town [15] and WHO estimates of tuberculosis prevalence[16] we assumed a prevalence of tuberculosis in the control arm of 1%. We powered our study in order to be able to detect a 30% reduction in prevalence of tuberculosis due to each intervention individually and a further 30% reduction in tuberculosis prevalence when the two interventions are combined. To achieve 80% power of detecting a significant difference (2-sided p < 0.05), an assumed between-community coefficient of variation *k *= 0.20 and 5,000 individuals sampled per community (Tab 1 and figure 2) we would need 12 communities in each arm. The total sample size will therefore be 24 communities, 6 in each of the four arms[17].

**Table 1 T1:** Sample size calculations for power of 80% (two-sided, 5% significance level), based on sample of 5000 individuals per community and allowing for 20% losses, for each of the main comparisons (ECF vs non-ECF & HH vs non-HH)

Prevalence (%) in Control arm	Reduction in Prevalence due to each intervention (ECF or HH) individually	Prevalence (%) in ECF or HH arm	Overall number of communities needed (equally split into 4 arms)

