### Analytic plan

As a community randomised trial ZAMSTAR will be analysed both at the cluster level, by deriving summary statistics for each community, and at the individual level using data from each individual in each community. For these analyses statistical methods that take account of between- and within-cluster variation will be used. The analysis will give each community equal weight. There are three intervention comparisons that will be made assessing the effects of ECF alone (12 Vs 12 communities), HH alone (12 Vs 12 communities) and ECF plus HH combined (6 Vs 6 communities). Impact measures of the above comparisons will be based on ratios.

To account for the study design, suitable generalized linear models will be used, where appropriate, to allow for clustering by community. For the binary outcomes (prevalence, incidence) the overall risk/rate for each cluster will be calculated. Risks/rates for each cluster will be shown, by strata and arm. A log transformation to normalise data will be applied to the risk/rate for each cluster. The mean and SD of these log risks/rates will be used to obtain the geometric mean (if the log transformation is clearly inappropriate the arithmetic mean will be used instead) and associated 95% CI for each intervention arm of the study. Linear regression of the log mean risk/rate on strata and arm will be used to estimate the relative risk/rate and 95% CI associated with the intervention. The approximate variance for the mean risks/rates ratio is obtained based on the residual mean square from a two-way analysis of variance (ANOVA) of community log-risk on stratum and study arm. A 95% CI for the relative risk/rate will be calculated from this variance using a t-statistic with 16 degrees of freedom (df) for the two main comparisons and 10 df for the comparison of arm 4 Vs arm 1.

For the continuous outcomes such as intervention costs and stigma levels, the overall mean for each community will be calculated, and means for each community will be shown, by strata and arm. The arithmetic mean and SD of these mean scores/numbers and associated 95% CI for each intervention arm of the study will be calculated. Linear regression of the mean score/number on strata and arm (2-way ANOVA on intervention and strata) will be used to estimate the difference in score/number and 95% CI associated with the intervention.

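### Fitting community-level confounders in a first stage without arm, then leaving them out of the second stage, shrinks the adjusted effect toward the null when those factors are imbalanced

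*Protocol article*

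**What the plan says.** All of this is in the protocol article, mostly in the Analytic plan.

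- **Confounders.** Three are named: age and sex, which are individual-level, and TST prevalence at baseline, which is community-level. Further factors may be added, described as follows: "as well as other factors found to differ between study arms at baseline and which may be risk factors for a particular outcome". The number and level of these further factors are not fixed.
- **First stage.** The plan states that "logistic regression will be used to adjust for confounders at the individual level and cluster level, adopting a two-stage process". Arm is left out at this stage: "The regression model will include terms for the adjustment factors and strata, but not study arm". The fitted model gives an expected count for each community.
- **Second stage.** "Linear regression of the log mean O/E on strata and arm (2-way ANOVA) will be used to estimate the risk/rate ratio and 95% CI". No adjustment factor appears here.
- **Variance.** It comes from the second-stage ANOVA: "The variance for the ratio of mean O/E is calculated from the residual mean square from an ANOVA of O/E on strata and arm".
- **Degrees of freedom.** For the crude analysis, 16 df are given for each main comparison and 10 df for arm 4 against arm 1. None are given for the adjusted analysis.
- **Size and allocation.** "The total sample size will therefore be 24 communities, 6 in each of the four arms". Under Randomization, allocation was stratified by country and high or low TST prevalence. It was also restricted on TST prevalence, HIV prevalence, urban/rural status, social context and location.

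**The concern.** The two-stage method suits individual-level factors, which should explain little of the difference between arms. A community-level factor is different. With 24 communities it can be correlated with arm by chance, and a first-stage model without arm then credits part of the intervention effect to that factor. The second stage cannot recover that part, because the factor is no longer in the model.

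The selection rule makes this worse. Factors enter because they differ between arms, which is the property that drives the shrinkage.

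A real effect could therefore be under-reported in the adjusted result. Readers could take an adjusted ratio closer to 1 than the crude one as evidence that confounding explained part of the effect, when the procedure itself had removed it.

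**Working it through.** **1. The plan's setting.** The standard formula for comparing cluster proportions is

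c = 1 + (z₀.₉₇₅ + z₀.₈₀)² × [p₀(1−p₀)/m + p₁(1−p₁)/m + k²(p₀² + p₁²)] / (p₀ − p₁)².

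The Sample size section gives p₀ = 0.0085, p₁ = 0.00595, m = 5,000 and k = 0.20. The bracket is 1.686×10⁻⁶ + 1.183×10⁻⁶ + 4.306×10⁻⁶ = 7.175×10⁻⁶, and (p₀ − p₁)² = 6.503×10⁻⁶. So c = 1 + 7.849 × 1.103 = 9.66 per side. Doubling and dividing by 0.8 for losses gives 24.2, against the stated 24. The check below therefore uses 24 communities, k = 0.20 and a true ratio of 0.70 (log ratio −0.357).

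**2. The mechanism.** Let a and Z be arm and the community-level covariates after removing strata, and let M be the projection that removes Z. The first stage leaves MY. Regressing MY on a gives a′MY/(a′a). Since MZ = 0, its expectation is

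β × a′Ma/(a′a) = β(1 − R²).

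This is exact for linear least squares and approximate for the plan's logistic first stage. For a covariate left to chance, 24 communities less 4 strata leave 20 dimensions, so R² is about 1/20 = 0.05 each.

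**3. Simulation of the written procedure.** First stage: logistic, without arm. Second stage: log O/E on strata and the two interventions, with t on 16 df. The comparison is one second-stage regression that also carries the covariates, with reduced df. Assumptions: 4 strata of 6, 4,000 evaluable per community, residual k = 0.20, and a log-prevalence slope of 0.15 per SD for each covariate. Imbalanced factors were picked from 8 candidates. There were 300 to 3,000 runs per row.

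| Community-level factors | R² | Mean log ratio: as written / joint | Quotient | Ratio as written | Coverage as written |
|---|---|---|---|---|---|
| 1, restricted | 0.007 | −0.366 / −0.369 | 0.99 | 0.693 | 94.9% |
| 3, restricted | 0.025 | −0.355 / −0.363 | 0.98 | 0.701 | 93.7% (300 runs) |
| 1, left to chance | 0.054 | −0.350 / −0.368 | 0.95 | 0.705 | 95.1% |
| 3, left to chance | 0.160 | −0.309 / −0.362 | 0.85 | 0.734 | 92.3% |
| 1, picked for imbalance | 0.128 | −0.325 / −0.368 | 0.88 | 0.723 | 94.3% |
| 2, picked for imbalance | 0.196 | −0.298 / −0.364 | 0.82 | 0.742 | 92.4% |
| 3, picked for imbalance | 0.254 | −0.278 / −0.365 | 0.76 | 0.757 | 91.2% |

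The quotient follows 1 − R² closely. The joint regression gives ratios of 0.69 to 0.70 and coverage of 94.0% to 96.1% in every setting with an effect. With three factors picked for imbalance, power is 57% as written and 70% with the joint regression.

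**4. A simpler version.** With a linear first stage on community log-risks, one factor left to chance gives 0.714, three give 0.739 (91% coverage), and three picked for imbalance give 0.771 (86%). A restricted factor gives 0.703 (95%). The joint regression gives 0.70 and about 95%.

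**5. No true effect.** In the logistic simulation, coverage as written is 94.9% to 96.7% and rejection is 3.3% to 5.1%. The reported standard error follows the actual spread of the estimate: with three factors left to chance, the SD is 0.100 and the mean SE 0.098.

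**The case against.** **It is an added analysis.** Crude effects are reported as well and are untouched. This stands, and it limits the weight of the point. The planned stratified permutation test is valid under the null but does not correct a shrunken estimate.

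**The design protects the named factor.** TST prevalence was both a stratum and a restriction factor. This stands: shrinkage there is about 1%. A reader might infer that every adjusted result is biased, but restriction also covered HIV prevalence, urban/rural status, social context and location. Age and sex should explain little of arm, though this was not simulated. The problem is confined to unrestricted, imbalanced community-level factors. The plan invites these without saying how many there will be, or that they will be community-level.

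**Degrees of freedom.** A reader might infer that the second stage ignores df spent in the first, so the interval is too narrow in itself and false positives rise. The null results in step 5 of the working contradict this. The 16 df are stated for the crude analysis and equal 24 − 2×4. Additive strata and arm would leave 17 to 19. An article may leave the adjusted df to the analysis plan.

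**Arm 4 against arm 1.** Worse figures are tempting here. With a true ratio of 0.49, one or two factors left to chance give about 0.53 and 0.56, with coverage of about 92% and 86%. They assume two strata and a first stage refitted on 12 communities. The Randomization section implies four strata, and the Analytic plan does not mention refitting. If one first stage uses all 24 communities, the figures are 0.508 (94%) and 0.526 (93%) without restriction, and 0.495 and 0.501 (94% to 95%) with it. The text does not settle which applies, so the worse figures cannot be relied on.

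**Conclusion.** The point holds in limited form. The article writes out both models and their terms, so this is a stated procedure and not a detail left to a fuller document. It shrinks the adjusted log ratio by about (1 − R²).

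- **TST prevalence and other restricted factors:** negligible.
- **One to three unrestricted community-level factors chosen for imbalance, true ratio 0.70:** about 0.72 to 0.77, with coverage of about 94% down to 86%. The lower end comes from the linear first stage with three factors. With 1,500 runs, the simulation error on coverage is about ±1.1 points (1.96 × √(0.95 × 0.05/1,500)), so the 94.3% for one factor cannot be told from nominal, while 92.4% and 91.2% can.
- **No true effect:** type I error is not inflated. The error is toward the null.

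The sizes rest on the assumed slope, four equal strata, 4,000 evaluable per community and selection from eight candidates, none of which the article fixes. The direction and the (1 − R²) factor do not depend on those choices. The procedure should be changed, because it performs worst when community-level adjustment is most wanted. It does not threaten the crude comparison.

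**What to change.** Keep only individual-level factors (age and sex) in the first-stage logistic model, with strata and without arm. Enter TST prevalence and any other community-level factor in the second-stage regression of log O/E, together with strata and arm. Take the interval from that regression's residual mean square, subtracting one residual df for each community-level factor.

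The cost is a few sentences of text and a few df in the adjusted analysis. With a restricted factor the loss is slight: simulated power was 83% with the joint regression against 84% as written. The Discussion says TB prevalence will not be measured until 2010, so on the article's own timeline the change can precede the outcome data.

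### The adjusted analysis of binary outcomes estimates the ratio from log(O/E) but takes its variance from unlogged O/E; read literally, this makes intervals modestly too narrow, mainly for HIV incidence

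*Protocol article*

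**What the plan says.** The rule is in the Analytic plan section of the protocol article, in the text on adjusted analyses of binary outcomes.

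- **First stage.** A logistic model gives expected events per community: "The regression model will include terms for the adjustment factors and strata, but not study arm". The observed-to-expected ratio is then formed, "and a log transformation applied to this ratio where appropriate".
- **Estimate and interval.** "Linear regression of the log mean O/E on strata and arm (2-way ANOVA) will be used to estimate the risk/rate ratio and 95% CI".
- **Variance.** The next sentence reads: "The variance for the ratio of mean O/E is calculated from the residual mean square from an ANOVA of O/E on strata and arm".

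In the crude analysis, the same section takes the variance from the "residual mean square from a two-way analysis of variance (ANOVA) of community log-risk on stratum and study arm", and the interval is formed "using a t-statistic with 16 degrees of freedom (df) for the two main comparisons and 10 df" for arm 4 versus arm 1. All analyses are also to be checked with a stratified permutation test.

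**The concern.** A difference in mean log(O/E) needs a standard error from the residual variation of log(O/E). The stated variance comes from the residual variation of O/E itself, which is a different quantity. The crude analysis uses one scale throughout, so the two analyses do not match.

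The two variances are close when O/E varies little around 1, and they separate when events per community are few. The rule covers every binary outcome, including sparse ones. HIV incidence is the sparsest outcome with its own power statement. At stake are the width of the adjusted intervals and, where p-values are read from them, the 5% two-sided error rate on which the trial is planned.

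**Working it through.** The plan gives no figure for the width or coverage of the adjusted intervals, so there is none to reproduce. The inputs below come from its Sample size section.

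**1. Check of the number analysed.** Use c = 1 + (1.96 + 0.84)² × [p0(1−p0)/n + p1(1−p1)/n + k²(p0² + p1²)] / (p0 − p1)², with 0.85% versus 0.595% and n = 5,000 × 0.8 = 4,000. At k = 0.15, c is about 8.3, so 9 per side and 18 in total, as in Table 1. At k = 0.20, c = 10.53, so 11 per side and 22 in total, against 24 in the plan. This is close enough to accept 4,000 per community.

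**2. Expected events per community.**
- TB prevalence: 4,000 × 1% = 40 in arm 1; 4,000 × 0.85% = 34 on the control side of a main comparison.
- TST conversion: 800 × 0.8 = 640 children; 640 × 3% = 19.2.
- HIV incidence: 150 households × 2-3 adults × 0.8 = 240-360; × 2.1% = 5.0-7.6. After the planned 40% reduction this is 3.0-4.5.

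**3. Size of the mismatch in one community.** The first-stage model contains strata but not arm, so O/E averages about 1 within a stratum and var(O/E) ≈ 1/m + k², where m is the expected number of events. The variance of the log was computed from the matching gamma-Poisson distribution at k = 0.20, with zeros set to 0.5.

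| Outcome | m | 1/m + k² | var(log) | SE ratio |
|---|---|---|---|---|
| TB, arm 1 | 40 | 0.0650 | 0.0691 | √(0.0650/0.0691) = 0.97 |
| TST | 19.2 | 0.0921 | 0.1031 | √(0.0921/0.1031) = 0.945 |
| HIV, 2.5 adults per household | 6.3 | 0.1987 | 0.2774 | √(0.1987/0.2774) = 0.846 |

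The unlogged variance is the smaller in each case, and the gap grows as events become fewer.

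**4. Simulation of the two-stage analysis.** There were 20,000 trials per setting, with 24 communities, gamma-Poisson counts, E from stratum means without arm, and log(O/E) regressed on stratum and both interventions. Intervals used t on 16 df. The standard error came either from the ANOVA of log(O/E) or, literally as written, from the ANOVA of O/E.

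| Outcome (main comparisons) | Narrower by | Coverage, mixed scales | Coverage, log variance |
|---|---|---|---|
| HIV incidence (k 0.1-0.2) | about 10-15% | about 90-92.5% | about 95% |
| TST conversion (k 0.20) | about 4-6% | about 94% | about 95% |
| TB prevalence (k 0.20) | 3-4% | 94-95% | about 95% |

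Null type I error for HIV under the literal rule is about 7.5-9%. Allowing k from 0 to 0.2 widens the HIV ranges to 8-17% narrower and 89-93% coverage.

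**5. Both parts unlogged.** Take the ratio of arithmetic means, with the unlogged mean square divided by the squared arm means. Coverage is then 95-97%. Null type I error is 3.8-4.3% for HIV, 4.2% for TST and 4.3% for TB. Those intervals are not too narrow.

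**The case against.** The strongest defence is that a coherent reading exists. The log is conditional, and the disputed sentence speaks of a ratio of mean O/E. For a ratio of arithmetic means, an unlogged residual mean square is the right ingredient, and step 5 shows no shortfall. The preceding sentence also assigns the CI to the log regression, which has its own log-scale residual, so the variance sentence may simply have lost the word log.

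This stands in part: the direction of error is fixed only on the literal reading. It does not clear the text. The plan specifies a logged estimate, and it neither says that the estimate changes scale when the log is dropped nor mentions division by squared arm means. Different readings give different intervals.

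The defence is also right that HIV is where the log is least secure. At k = 0.20 with the planned reduction, at least one community has zero events in about 57% of trials at 5.0 events and 18% at 7.6, and log(O/E) is then undefined. An unlogged analysis might well be used there. That is a reason to write out both routes.

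The permutation test does protect the p-values, but it does not correct a reported CI.

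A reader might infer that all adjusted intervals are seriously too narrow, or that the primary result is compromised. The documents do not support that. The main TB comparisons lose about one point of coverage or less at the design values, and the crude analysis is specified correctly.

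**Conclusion.** The sentence is wrong as written: it pairs a log-scale estimate and interval with a variance from the unlogged scale, and it departs from the crude analysis in the same section. On the literal reading the consequence is modest. It is minor for the primary outcome, small for TST conversion, and material mainly for HIV incidence.

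Calling the HIV intervals badly wrong would go too far. Coverage there is about 90-92.5%, and that rests on assumptions outside the document: k of 0.1-0.2 (no k is stated for HIV), zeros set to 0.5, four strata of assumed size (8, 8, 4 and 4, or 6 each), no covariates beyond strata, and no clustering within households. The size is not established for any reading in which the estimate is also unlogged.

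**What to change.** Replace the variance sentence with two rules.

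1. Whenever the log is used, the variance of the log ratio comes from the residual mean square of an ANOVA of log(O/E) on stratum and arm, matching the crude analysis.
2. Where the log is not appropriate, for example when a community has zero events, the estimate and the variance are both taken on the unlogged scale, as a ratio of arithmetic means, with the variance formula stated.

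The cost is a sentence or two, with no change to design, sample size or data collection. Adjusted intervals become slightly wider for TB prevalence and TST conversion, and noticeably wider for HIV incidence.
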